#### 2.11.2. Qualitative Data

Qualitative interviews will be analyzed with content analysis as described by Mayring [55], adhering to the guidelines of thematic analysis [56]. Therefore, a team of researchers will first deduct possible categories through an analysis of the literature and then test this set of categories with 5–10% of the interviews and develop new categories from the interviews (bottom-up). In consensus meetings, the final set of categories will be defined and tested with the next 10% of interviews to rate the amount of concordance between the different raters. Qualitative and quantitative data will be related to each other to identify categories that are related to improvement.

### 2.12. Ethical Considerations

The authors assert that all procedures contributing to this work comply with the ethical standards of the relevant national and institutional committees on human experimentation and with the Helsinki Declaration of 1975, as revised in 2008. All procedures involving human participants were approved by the responsible Ethics Committee of the Antonine University Baabda (approval number 279-2022 in February 2022). 

Informed consent is being obtained from all study participants before they enroll in the study. For minors, consent is being obtained along with written parental or caregiver consent. When the data are analyzed and the results of the study are published, the names and identities of the participants will not be used. Participants are free to leave the study at any time without supplying a reason and with no further consequences.

In case of an accident requiring medical treatment during the intervention, the participant will be taken to an appropriate medical care provider. Fees will be paid by ClimbAID and the insurance of its Lebanese partner Arcenciel (owner of the land and the facility).

Definition of adverse events (AEs): Mild AEs in the IG: all sorts of bruises or scratches or other minor superficial injuries that are transient and do not require treatment;Moderate AEs: injuries that are transient but require medical treatment, such as ligament ruptures or sprains, broken bones in legs or arms;Severe adverse events (SAEs): severe head injuries, spinal cord injuries, death, suicide attempts.

Termination rules: If an SAE occurs in the IG during the intervention, the program will be terminated if the intervention is determined to be directly responsible for the SAE.

In the case of moderate AEs, the intervention will be terminated if there are three more AEs in the intervention than in the waitlist group, if the AEs are determined to be a direct result of the intervention. Mild AEs will be recorded but will not result in the termination of the program.

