### 2.7. Sample Size Estimation

Power calculation was performed using G*Power software [48] (University of Duesseldorf, Germany) with a two-tailed alpha of 0.05, a beta of 90%, and an estimated effect size of Cohen’s d = 0.55. This resulted in a necessary sample (as treated AT) of at least 52 members per group at posttest. 

As the dropout rate is difficult to foresee in the current political and economic situation, we assumed a drop-out rate of 35% per intervention cycle. Thus, we need to enroll 80 participants in the IG and the CG, respectively. Hence, at least 160 adolescents need to be included in the study, distributed across the six climbing groups (each consisting of 12–14 participants) and the control group. Including the waitlist-control group (which will be offered the intervention after the study period), up to a total of 160 adolescents should thus be provided with a climbing program. Figure 2 gives an estimated overview about sample sizes.

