The climbing intervention has a slight risk of injury, comparable to the risk involved in other sport interventions. In previous studies conducted by our own research group with around 5000 bouldering hours, no severe adverse events have occurred. Nevertheless, any accidents and potential AEs, including suicidal behavior or accidents resulting in injuries, will be documented by the trainers/facilitators for the IG and by the study headquarters for the CG. Regular interim evaluations will be made, and in the case of SAEs in the IG, the intervention will be terminated. As with any activity involving transportation in a motor vehicle, there is always a risk of injury, permanent damage, or death from accidents. The responsible NGO always tries to keep the risk of accidents as low as possible and therefore only works with reliable and trustworthy transportation service providers who comply with the relevant legal provisions and safety regulations. Participants are brought by exclusive buses to and from the intervention, and the bus driver is accompanied by ClimbAID staff to provide a safe environment for all participants, especially female participants. In the case of an AE requiring medical treatment, ClimbAID will cover the patient’s costs, thus ensuring adequate treatment.

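### As worded, a climbing-caused injury with permanent impairment outside the four listed SAEs has no adverse event class and triggers neither termination rule

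*Protocol article*

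**What the plan says.** Section 2.12 (Ethical Considerations) of the protocol article defines three classes of adverse event:

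- Mild: bruises, scratches or other "minor superficial injuries that are transient and do not require treatment".
- Moderate: "injuries that are transient but require medical treatment, such as ligament ruptures or sprains, broken bones in legs or arms".
- Severe (SAE): "severe head injuries, spinal cord injuries, death, suicide attempts".

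The termination rules follow in the same section. For an SAE in the intervention group, "the program will be terminated if the intervention is determined to be directly responsible for the SAE". For moderate events, the intervention is to be "terminated if there are three more AEs in the intervention than in the waitlist group", provided the events are a direct result of the intervention. Mild events are recorded and never stop the programme.

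The Discussion adds that accidents and adverse events will be documented in both groups and that regular interim evaluations will be made. Its own stopping statement is that "in the case of SAEs in the IG, the intervention will be terminated".

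**The concern.** A stopping rule should respond at least as strongly to graver harm as to lesser harm. Here the two lower classes are both limited to transient injuries, and the top class is a short list with no general description of what makes an event severe. That leaves room for an injury too lasting to be moderate and not named among the SAEs. If climbing caused it, neither rule calls for a stop, although three excess sprains that heal would.

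What is at stake is the safety of participants aged 14 to 19 (section 2.3), not the trial's result. The waitlist group is to be offered the same programme after its waiting period (sections 2.2.3 and 2.5), so the rules also bear on whether a second set of adolescents is exposed after such an event.

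**Working it through.** The article gives no figure to reproduce. The check takes each kind of injury through the definitions in section 2.12 and then through the termination rules. Throughout, the event is assumed to be a direct result of climbing, with no moderate event in the waitlist group.

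**Step 1: class.**
- Transient, superficial, untreated: mild.
- Transient, treated: moderate. The examples are open, since they are introduced as examples.
- One of the four named items: SAE. Unlike the moderate class, this list has no wording that marks it as examples and no general criterion.
- Permanent and not one of the four items: not mild and not moderate, because both require transience; not an SAE, because it is not named.

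**Step 2: rule.**
- One severe head injury: one SAE, so terminate.
- Three healing sprains: excess of 3 − 0 = 3 moderate events, so terminate.
- One healing arm fracture: excess of 1 − 0 = 1, below three, so no termination.
- One lasting loss of sight: 0 SAEs and 0 moderate events, so no termination under either rule.

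The last case is the gap. The others behave as intended. This is a reading of the text set out in order; it is not evidence on how often such cases arise.

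**Step 3: does another section close it?** The Discussion ensures the injury would be written down and could come up at an interim evaluation. It gives the injury no class, and its stop trigger is again the SAE. Its sentence on SAEs also omits the causality condition in section 2.12, but that makes no difference here, because both statements depend on the event being an SAE.

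**Step 4: who could be exposed afterwards.** Section 2.7 plans 80 participants per group and says that "up to a total of 160 adolescents should thus be provided with a climbing program". The waitlist share is 160 − 80 = 80. This is a ceiling on people offered the programme, since their participation is voluntary (section 2.2.3). It is not a count of people harmed.

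**The case against.** The strongest reply is that calling the SAE list closed is an inference. The section sets out a scale from mild through moderate to severe and nowhere says that only these four items count. Since the moderate class ends at transient injuries, a sensible reader would treat anything worse as severe. It can be added that the article condenses a protocol that is not shown, that the group reports no severe events in around 5000 bouldering hours, and that documentation and interim evaluations would bring a grave injury to attention.

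Part of this stands. Staff might well classify such an injury as severe, and the gap is shown only for the article's wording. But the article itself prints both the definitions and the rules that depend on them, so this is a rule stated poorly and not a detail left out. Stopping rules are fixed in advance so that the gravest cases are not left to interpretation on the day.

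A reader might infer more than the text supports:

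- *That a life-threatening injury that heals is also unclassified.* It is not. If it is transient and treated, it is moderate. Moving it to the SAE class would be a stricter threshold, not the closing of a gap.
- *That limb fractures or ligament ruptures with lasting damage show the same gap.* These are named as moderate examples and might in practice be counted there despite the word transient, so they are not clean examples.
- *That the article itself foresees permanent harm from climbing.* The Discussion does say "there is always a risk of injury, permanent damage, or death from accidents", but the subject is motor vehicle transport. For climbing it describes only a slight injury risk.
- *That the programme would be obliged to continue.* The rules say when it must stop. They do not forbid stopping otherwise, though no section states a discretionary power to do so.

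**Conclusion.** The point holds in its narrow form. As written, a climbing-caused injury with permanent impairment, outside the four listed SAEs and outside the injuries named as moderate, has no class and triggers neither termination rule, while three excess transient moderate events do. The stated rules are therefore not ordered by gravity of harm.

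The size is minor. No efficacy result changes. The documents give no frequency for such injuries, and none is claimed. Table 1 lists recruitment as complete, so the benefit is confined to sessions still to run, including those offered to the waitlist group. The conclusion rests on reading the SAE list as exhaustive, which its wording supports but does not state outright.

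**What to change.** Add to the SAE definition in section 2.12: *or any other injury causing, or expected by the treating clinician to cause, significant permanent impairment*. The clinician's expectation is needed because permanence may not be established within an 8-week intervention; the word significant keeps trivial residual effects from forcing a stop.

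Apply the existing SAE rule of section 2.12, so that the programme ends if the intervention is found directly responsible. Healing sprains, ligament ruptures and limb fractures stay moderate under the existing rule of three excess events. Including life-threatening injuries that heal is an optional tightening that the sponsor may consider separately.

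The cost is one sentence of wording and a notification to the ethics committee, with no new data, staff or participants. The downside is that a single such event caused by climbing could end the programme before all waitlist participants have received it.

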The CG initially receives no climbing intervention, but all participants are rewarded with 100,000 LBP (between $2.80 and $3.60 USD depending on the daily rate) after completing the posttest. After completing the IG-CG climbing cycle (8 weeks), participants in the CG will also be given an opportunity to participate in the YouCLIMB program.

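### Section 2.12 and the Discussion give opposite actions for a severe adverse event in the intervention group that is judged not to be caused by the intervention

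*Protocol article*

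**What the plan says.** The termination rules stand in section 2.12 (Ethical Considerations). The most serious class is defined as "Severe adverse events (SAEs): severe head injuries, spinal cord injuries, death, suicide attempts". For such an event in the intervention group (IG) during the intervention, "the program will be terminated if the intervention is determined to be directly responsible for the SAE".

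The Discussion, in its paragraph on risk, mentions regular interim evaluations and continues: "in the case of SAEs in the IG, the intervention will be terminated". It sets no causality condition and does not refer back to section 2.12.

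For moderate events section 2.12 says that "the intervention will be terminated if there are three more AEs in the intervention than in the waitlist group", and adds the condition "if the AEs are determined to be a direct result of the intervention". This rule appears nowhere else. Section 2.5 describes the comparison group (CG) during the same period: "The CG initially receives no climbing intervention".

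**The concern.** A termination rule has to give one answer for one event. Here the answer for an SAE depends on which section is consulted. Site staff, an ethics committee or a guardian who reads the Discussion would expect the intervention to end after any SAE in the IG. Someone who works from section 2.12 would first ask whether the intervention caused it.

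The events on which the two texts part are foreseeable. The SAE definition covers death and suicide attempts, which need not come from climbing. The Discussion lists suicidal behaviour among the events to be documented and names transport accidents as a risk. It also puts the share with at least one psychiatric diagnosis at about 55% of Syrian refugee adolescents and at least 30% of Lebanese youth, and it confirms that no exclusion criterion concerns diagnosis or distress. A wrong or disputed decision would affect participants' safety in one direction and completion of the trial in the other.

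The moderate-event rule raises a smaller question. It compares two arms and also asks for attribution to an intervention that only one arm receives.

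**Working it through.** No arithmetic in the article underlies either rule, so the check is a comparison of texts.

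**SAE rule.** Take an SAE in the IG during the intervention and apply each text.

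| Causality judgement | Section 2.12 | Discussion |
|---|---|---|
| Intervention directly responsible | terminate | terminate |
| Intervention not directly responsible | condition not met, no termination under this rule | terminate |

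The first row agrees and the second does not. Strictly, section 2.12 says *if* rather than *only if*, so it could be called silent on the second row. But the clause has a function only if failing the condition means that the rule does not end the programme. If the programme ended either way, the clause would be redundant. Read as a rule, section 2.12 conflicts with the Discussion in the second row.

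**Moderate-event rule.** Let *a* be the IG moderate events judged a direct result of the intervention, *u* the other IG moderate events, and *w* the CG moderate events. The CG does not climb in this period (section 2.5), so none of the *w* events can be a direct result of the intervention. The text allows three readings:

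1. Attribution decides which events count in both arms. The CG count is then 0 and the trigger is *a* − 0 ≥ 3.
2. Attribution decides which events count in the IG only. The trigger is *a* − *w* ≥ 3, that is *a* ≥ 3 + *w*.
3. All events count in both arms and attribution is a second condition. The trigger is *a* + *u* − *w* ≥ 3, followed by the attribution judgement.

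Hypothetical counts, chosen only to show where the readings separate:

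| *a* | *u* | *w* | Reading 1 | Reading 2 | Reading 3 |
|---|---|---|---|---|---|
| 3 | 0 | 0 | 3 − 0 = 3, met | 3 − 0 = 3, met | 3 + 0 − 0 = 3, met |
| 3 | 0 | 1 | 3 − 0 = 3, met | 3 − 1 = 2, not met | 3 + 0 − 1 = 2, not met |
| 3 | 1 | 1 | 3 − 0 = 3, met | 3 − 1 = 2, not met | 3 + 1 − 1 = 3, count met, attribution still to be judged |

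The readings coincide when every IG event is attributed and the CG has none. One CG event is enough to separate them. The article gives no expected rate of moderate events, so no probability is attached to this.

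**The case against.** The strongest reply on the SAE rule is that section 2.12 holds the formal rules, with definitions and conditions, and that the Discussion clause merely shortens them in a paragraph about risk. This is a possible account of how the difference arose, and it is true that the texts differ only for SAEs not attributed to the intervention. It does not remove the conflict. The Discussion sentence is not written as a summary or a cross-reference. It states an action, and links it to interim evaluations that the termination rules in section 2.12 do not mention. The article may condense a fuller protocol, but this is not a detail left out: it states both rules.

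On moderate events the reply largely succeeds. A reader might infer that this rule, too, leads to opposite decisions, or that it cannot work because an unexposed arm has no attributable events. The documents do not support that. The rule appears once and nothing contradicts it, and reading 3 above is workable: the all-cause excess nets out background injury and attribution acts as a second gate. What remains is that the text does not say which reading is meant.

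A reader might also infer that the arm counts are not comparable, because events are documented "by the trainers/facilitators for the IG and by the study headquarters for the CG". That shows only that the recorder differs by arm. The article does not say how or how often the study headquarters follows up the CG, and a condensed article may leave this to the full protocol. Nor would adverse-event items in the posttest questionnaire help: the posttest comes immediately after the intervention ends (section 2.2.3), too late to inform termination within that cycle.

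**Conclusion.** The SAE inconsistency holds as the article is written. Two current passages prescribe opposite actions for one class of event: an SAE in the IG judged not to be directly caused by the intervention. For SAEs that are attributed to the intervention there is no conflict. The conclusion rests on the wording alone and on taking the causality clause in section 2.12 as having effect. It needs no assumption about event rates. It does not touch the sample size or the analysis of outcomes. Its weight comes from participant safety and from whether the trial runs to completion.

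The moderate-event point is secondary. It is an ambiguity within a single rule, and it changes the trigger only when the CG has moderate events or the IG has unattributed ones.

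Which SAE rule or which moderate-event reading is right is not judged here.

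**What to change.** Reconcile section 2.12 and the Discussion into one SAE termination statement, used in the same words in both places, that makes explicit whether a causality judgement is part of the rule. If the full protocol already holds a single rule, bring both passages of the article into line with it. The content is for the sponsor and the ethics committee.

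In the moderate-event rule, state which events enter the count in each arm, and whether attribution decides what is counted or is a separate condition applied after the count.

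The cost is a change of wording with notification of the ethics committee. No data collection changes. Table 1 lists recruitment as complete, so the reconciled statement should reach the people who apply the rule in any cycle still running.

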## 3. Discussion

This is the first study to investigate the effect of a psychosocial bouldering intervention with adolescent refugees. The intervention is being carried out in Lebanon, which is one of the countries with the highest per capita intake of refugees [2] and will therefore contribute to knowledge about the situation of refugees in low/middle income countries [38]. With a waitlist-control-group design, all participants will be able to benefit from the opportunity at no cost. The existing literature shows that many Syrian refugees do not meet the WHO’s physical activity guidelines [57]. About 55% of Syrian refugee adolescents [2] and at least 30% of Lebanese youth [58] experience at least one psychiatric diagnosis, such as depressive symptoms, anxiety, PTSD, or related symptoms (e.g., sleeping disorders). In addition to the psychosocial intervention provided in a safe and protected environment, participants may also profit from the increased physical activity.

The results of the study may contribute to knowledge about sport interventions and their effects on psychological well-being. Knowledge regarding novel, low-threshold intervention to support adolescent refugees residing in disadvantaged surroundings is urgently needed. 

The climbing intervention has a slight risk of injury, comparable to the risk involved in other sport interventions. In previous studies conducted by our own research group with around 5000 bouldering hours, no severe adverse events have occurred. Nevertheless, any accidents and potential AEs, including suicidal behavior or accidents resulting in injuries, will be documented by the trainers/facilitators for the IG and by the study headquarters for the CG. Regular interim evaluations will be made, and in the case of SAEs in the IG, the intervention will be terminated. As with any activity involving transportation in a motor vehicle, there is always a risk of injury, permanent damage, or death from accidents. The responsible NGO always tries to keep the risk of accidents as low as possible and therefore only works with reliable and trustworthy transportation service providers who comply with the relevant legal provisions and safety regulations. Participants are brought by exclusive buses to and from the intervention, and the bus driver is accompanied by ClimbAID staff to provide a safe environment for all participants, especially female participants. In the case of an AE requiring medical treatment, ClimbAID will cover the patient’s costs, thus ensuring adequate treatment.

The strengths of the study are the large sample size, the existence of a control group, the mixed-methods approach, the use of manualized treatment options, the naturalistic setting, and therefore, the pragmatic nature of the evaluation of a real-world program. One limitation is the lack of randomization. In this specific study, randomization may also have been a limitation because it may have resulted in the exclusion of female participants for cultural reasons. Being female in a refugee context is a risk factor for mental distress, especially depression [38]. Syrian refugees in Lebanon often live according to religious or cultural traditions with a strong desire to protect girls from potential harmful encounters outside the family. To include female participants, we decided not to randomize the group to allow family members who also need to comply with the inclusion criteria (e.g., mostly brothers, sisters, cousins) to participate together in the same intervention group. In addition, we offered female-only groups, and ClimbAID staff travel on the buses that collect all the participants from their homes. No participants must use public transportation. We therefore concluded that the disadvantages of randomization (which would prevent a vulnerable group from participating in the intervention) outweighed the positives. If the groups differ at baseline in relevant factors, appropriate statistical methods (e.g., propensity score matching) will be applied.

Another potential limitation is that the bouldering intervention cannot be blinded with respect to facilitators or participants. All outcome measures are self-assessed and, therefore, are also not blinded. Third, in the absence of exclusion criteria regarding possible diagnoses or levels of psychological distress, it is possible that we will obtain a heterogeneous sample, with the associated advantages of a naturalistic design and low-threshold intervention and the disadvantages of potentially diluted intervention effects.

